## Abstract

**Background::**

Acute respiratory distress syndrome (ARDS) is an increasingly common acute respiratory failure that seriously threaten people's health. ARDS has a case fatality rate of up to 40%. ARDS is a serious threat to the life safety of patients and the quality of life, causing a huge economic burden to individuals, families and society. ARDS has become a large worldwide public health problem. Prone position ventilation (PPV) is an important auxiliary treatment for ARDS, which could improve oxygenation. However, PPV could cause Pressure injuries (PI) and other complications easily. We found that 45° PPV could reduce the incidence of PI, but lack of robust Evidence-based medicine evidence proving its efficacy. Therefore, we designed a randomized controlled trial to evaluate the efficacy of 45° PPV in the treatment of ARDS.

**Methods::**

A total of 268 patients will be randomly assigned to the control group and the test group (n = 134 each) in a ratio of 1:1. The treatment period is 7 days. The primary outcome measure will be the incidence of PI. The secondary outcomes will include APACHE II score, Braden Scale score, heart rate, systolic blood pressure, diastolic blood pressure, central venous pressure, mean arterial pressure, pH of arterial blood, oxygenation index, oxygen partial pressure, and carbon dioxide partial pressure. The evaluation will be performed at baseline, 1 hour, 12 hour, 48 hour, 5days, 7days after PPPV.

**Results::**

This study is helpful to evaluate the efficacy of 45° PPV in the treatment of ARDS.

**Conclusion::**

45° PPV may reduce the incidence of PI and improve oxygenation in patients with ARDS, which has important value in practical application

**Trial registration::**

ChiCTR2000040436, registration time: November 28, 2020.

## Introduction

1

Acute respiratory distress syndrome (ARDS) is an increasingly common acute respiratory failure that seriously threaten people's health. ARDS has a case fatality rate of up to 40%.^[1,2]^ The concept of adult respiratory distress syndrome was first proposed by Ashbaugh et al in 1967.^[3]^ With the continuous understanding of ARDS, it was found that ARDS occurs not only in adults but also in children, The American Thoracic Society (ATS) and European Society of Intensive Care Medicine have renamed adult respiratory distress syndrome as ARDS.^[4,5]^

ARDS is a clinical syndrome characterized by acute, progressive dyspnea and intractable hypoxemia, which is caused by various intrapulmonary and/or extrapulmonary causes other than cardiogenic factors. ARDS is an acute respiratory failure caused by diffuse alveolar and interstitial edema following the damage to pulmonary capillary endothelial cells and alveolar epithelial cells. ARDS is characterized by progressive dyspnea and intractable hypoxemia, non-cardiogenic pulmonary edema, opacity of bilateral chest X-ray films and decreased lung compliance. The etiology of ARDS includes shock, severe infection, trauma, severe burn, pancreatitis, pneumonia, drug overdose and poisoning, blood transfusion, etc.^[6–9]^

Piehl et al^[10]^ first reported the efficacy of prone position ventilation (PPV) in ARDS, and he found that PPV can improve oxygenation by recruiting alveoli situated in dorsal dependent regions, which is consistent with the results of subsequent clinical studies.^[11–13]^ PPV could improve the pulmonary ventilation/blood flow ratio, oxygenation and reduce the mortality by recruiting alveoli situated in dorsal dependent regions and promoting the redistribution of lung gas.^[14–17]^ One meta-analyses have shown that PPV could reduce mortality in patients with severe ARDS.^[12]^ Gueirn et al.^[15]^ found that early application of PPV can significantly reduce the 28-day and 90-day mortality rate mortality in patients with severe ARDS. More than 70% of lung injury patients could clinically improve oxygenation by using PPV.^[18]^

However, a clinical application of PPV is difficult especially for critically ill patients with various pipelines and obese patients. Even worse, PPV could cause a variety of complications, such as hemodynamic instability, pressure injuries (PI), aspiration, conjunctival edema, as well as the compression, displacement and prolapse of various indwelling catheters caused by postural changes, among which the PI is the most common. Manzano et al.^[19]^ found that the incidence of PI in patients with mechanical ventilation for more than 7 days was as high as 35.6%. Mechanical ventilation time was a risk factor for PI in critically ill patients.^[20,21]^ Sud S et al^[22]^ found that the incidence of PI was 42.7% in patients with ARDS using PPV.

We found that 45 °PPV could reduce the incidence of PI, but lack of robust Evidence-based medicine evidence proving its efficacy. Therefore, we aim to conduct a randomized controlled clinical trial (RCT) to evaluate the efficacy of 45 ° PPV in the treatment of ARDS.

## Methods

2

### Trial design and registration

2.1

This is a randomized controlled clinical trial of 45° PPV (test group) compared to 0° PPV (control group). Participants will be recruited from the Department of Emergency and Intensive Care Medicine, Guangzhou Panyu central hospital. The Figure 1 shows the study design in the flowchart, and the Figure 2 illustrates the time schedule of enrolment, interventions, assessments, and visits of participants. We developed the protocol based on the Standard Protocol Items: Recommendations for Intervention Trials guidelines (Additional file 1).

**Figure 1 F1:**
[figure not shown]
Study flow diagram.

**Figure 2 F2:**
[figure not shown]
Study design schedule.

This protocol has been registered in the Chinese Clinical Trial Registry on November 28,2020, http://www.chictr.org.cn/showprojen.aspx?proj=64955. And the registration number is ChiCTR2000040436.

### Patient population and eligibility criteria

2.2

#### Inclusion criteria

2.2.1

(1)Patients meet the Berlin diagnostic criteria for ARDS^[23]^;(2)Patients with ARDS require invasive mechanical ventilation;(3)The onset time of ARDS is less than 72 hours;(4)The age ranged from 18 to 75 years old;(5)Those who agree to participate in this study and are willing to sign informed consent.

#### Exclusion criteria

2.2.2

(1)Under 18 years old or over 75 years old;(2)Pregnant or breastfeeding women;(3)Patients with PI at admission;(4)Patients with contraindications for PPV including intracranial hypertension, recent maxillofacial/thoracic surgery, massive hemoptysis, spinal/pelvic instability, mean arterial pressure  < 65mm Hg;(5)Hemodynamic instability;(6)Severe pneumothorax;(7)The survival time is expected to be lower than 24 hours;(8)Previous or current confirmed diagnosis of pulmonary bullae, spontaneous pneumothorax and Chronic obstructive pulmonary disease;(9)There is active bleeding in the respiratory tract.

### Sample size

2.3

The sample size was calculated based on the incidence of 7-day PI. According to the previous literature,^[24]^ we hypothesized that the incidence of 7-day PI in the control group and the test group will be 42.7% and 22.7%, respectively. Set ɑ = 0.05 and □ = 0.10. We use PASS 15 software (PASS NCSs, LLC, USA) to calculate the size of the control group and test group, N1 = N2 = 111. Assuming that 20% of patients may be lost during follow-up, a total of 268 patients will be recruited.

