### Statistical analysis

3.10

Statistical analysis will be performed on an intention-to-treat-basis. The measurement data will be prestend

In this trial, we will conduct intention to treat analysis and protocol analysis. The measurement data will be expressed as mean ± standard deviation and the enumeration data will be expressed as in percentage. The student *t*-test will be performed for measurement data and chi square test or Fisher exact probability methods for enumeration data. All data statistics were conducted using a bilateral test, and statistical significance was set at *P* < .05. The clinical results will be analyzed by SPSS 22.0 statistical software (IBM SPSS statistics, IBM Corp, Somers, NY).

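### Minor arithmetic slip in section 2.3: the 20% loss allowance was added as 111 × 1.2, so 134 per arm leaves about 107 evaluable, not the calculated 111

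*Protocol article*

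**What the plan says.** The protocol article, section 2.3 (Sample size), assumes "the incidence of 7-day PI in the control group and the test group will be 42.7% and 22.7%, respectively". The error rates are given as "Set ɑ = 0.05 and □ = 0.10"; the second symbol did not survive text extraction. PASS 15 is then used "to calculate the size of the control group and test group, N1 = N2 = 111". The section does not name the test or the variance option.

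The step from 111 per arm to the recruitment target is one sentence: "Assuming that 20% of patients may be lost during follow-up, a total of 268 patients will be recruited". No inflation formula is given. The Methods paragraph of the abstract confirms the split: "A total of 268 patients will be randomly assigned to the control group and the test group (n = 134 each) in a ratio of 1:1".

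Section 3.10 (Statistical analysis) specifies two-sided testing ("All data statistics were conducted using a bilateral test, and statistical significance was set at" .05). It plans a chi-square or Fisher test for categorical outcomes and names an intention-to-treat analysis alongside a per-protocol one.

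**The concern.** Three statements in section 2.3 should fit together: 111 per arm are needed, 20% may be lost, and 268 are recruited. They do not. The recruited number looks like 111 raised by 20%, but taking 20% off that larger number removes more than was added. If the assumed loss occurs, each arm falls short of the size on which the power statement rests.

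This section is the only justification of the trial's size for the primary outcome, and readers will take its power, loss allowance and total as mutually consistent. The Discussion also names a high loss rate, due to the severity of illness, as a limitation. The loss allowance is therefore a working assumption of this trial.

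**Working it through.** **Inputs**
- Event rates: control p1 = 0.427, test p2 = 0.227, difference 0.20 (section 2.3).
- α = 0.05 (section 2.3), two-sided (section 3.10).
- β = 0.10, so power 90%. This is inferred: the symbol is lost and only the value 0.10 is legible.
- Calculated size: 111 per arm (section 2.3).
- Loss: 20%. Recruited: 268, or 134 per arm (section 2.3 and abstract).

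**Step 1. Reproduce 111.** The unpooled two-proportion z-test formula is

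n = (1.960 + 1.2816)² × [p1(1 − p1) + p2(1 − p2)] / 0.20²

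p1(1 − p1) + p2(1 − p2) = 0.427 × 0.573 + 0.227 × 0.773 = 0.2447 + 0.1755 = 0.4201

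n = 10.508 × 0.4201 / 0.04 = 110.4, so 111 per arm.

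This matches the plan and supports both inferences (β = 0.10 and the unpooled variance). For comparison, the pooled formula gives 113.5, so 114 per arm.

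**Step 2. Reproduce 268.**
- Adding 20%: 111 × 1.2 = 133.2, rounded up to 134 per arm, 268 in total. This matches the plan.
- Dividing the loss out: 111 / (1 − 0.20) = 138.75, rounded up to 139 per arm, 278 in total. This does not match; the difference is 278 − 268 = 10.

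**Step 3. What 268 leaves after 20% loss.**
- 134 × 0.8 = 107.2, about 107 per arm, or 4 fewer than 111.
- Check on the divided-out figure: 139 × 0.8 = 111.2, which is enough.
- Largest loss that still leaves 111 of 134: 1 − 111/134 = 17.2%.

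**Step 4. Effect on power** (42.7% v 22.7%, two-sided 5%).

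Unpooled z-test: power = Φ(0.20 / √(0.4201/n) − 1.960).
- n = 111: 0.20 / 0.06152 = 3.251; Φ(1.291) = 90.2%.
- n = 107: 0.20 / 0.06266 = 3.192; Φ(1.232) = 89.1%.

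| Basis | 111 per arm | 107 per arm | Lost to the slip |
|---|---|---|---|
| Unpooled z-test (reproduces 111) | 90.2% | 89.1% | 1.1 points |
| Pooled formula | 89.3% | 88.2% | 1.1 points |
| Chi-square without continuity correction, exact enumeration | 89.6% | 88.4% | 1.2 points |

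**Step 5. Keep the bases apart.** The 17.2% in step 3 belongs to the calculation that gave 111. On the pooled basis, which corresponds to the chi-square test, 114 per arm are needed, and 134 then tolerates only 1 − 114/134 = 14.9% loss.

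**The case against.** The best defence is scale. Four evaluable patients per arm and about one percentage point of power lie well within the uncertainty of the assumed event rates and of a loss rate that the plan itself words as a possibility. No analysis or decision changes. This stands, and it is why the point is minor.

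A second defence is that an intention-to-treat analysis keeps all 134 per arm. It does not repair the sentence, because section 2.3 itself budgets for lost patients. If nobody drops out of the analysis, no allowance is needed; if 20% do, the allowance is too small.

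A third is that the 20% was meant as a proportion of 111. The text speaks of 20% of patients being lost and says nothing of such a base. On that reading the implied loss among those recruited would be 22.2/133.2 = 16.7%, which is not the figure stated.

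It is also true that the unpooled method and the 90% power are inferred. The inflation slip does not depend on either: it follows from 111, 20% and 268 alone.

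A reader might infer something stronger, that power falls to about 85% because section 3.10 also names Fisher's exact test. The documents do not support this. Section 3.10 offers chi-square or Fisher, and Fisher is conventionally kept for small expected counts. Here the smallest expected cell with 107 per arm is about 107 × 0.227 = 24. Most of that gap also comes from the test and not from the loss formula: exact enumeration for Fisher gives 86.8% at 111 per arm and 85.4% at 107, so the slip again accounts for only 1.4 points.

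**Conclusion.** The point holds as a minor wrong figure. A requirement of 111 evaluable per arm, a 20% loss and a total of 268 cannot all be true. The allowance was added to 111 when it should have been divided out, which leaves about 107 per arm and a total 10 short of the 278 that the plan's own figures imply.

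Power with 20% loss is about 89% on the basis that reproduces 111, and about 88% with the planned chi-square test, against the intended 90%. These power figures assume the planned event rates, equal loss in both arms, β = 0.10 for the lost symbol and, for the 89%, an unpooled two-sided z-test.

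A reader might conclude that the trial is seriously underpowered or must be enlarged. The figures do not support that.

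**What to change.** Keep 268 and restate one figure in section 2.3, on one consistent basis. Either of these would do:

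1. Keep the calculation that gave 111 and state that 134 per arm leaves the calculated 111 evaluable if loss is at most 17%.
2. Keep the 20% loss and state that about 107 per arm are then evaluable, giving about 88% power with the chi-square test.

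Do not put the 17% next to a chi-square basis, since that basis needs 114 per arm and tolerates only 14.9% loss. No Fisher figure is needed. Whichever option is chosen, name the test and variance option behind the number, so that a reader need not infer them.

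The cost is one corrected sentence and a slightly less favourable loss allowance or power. No extra patients are needed, and the abstract's 268 and 134 per arm can stay. Recruiting 278 would also restore consistency, but a gain of about one percentage point of power does not make it necessary.

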### Randomization

2.4

Patients will be randomly allocated into either to the control group and the test group according to the ratio of 1:1. The random allocation sequence listing will be generated by SPSS software operated by a third party who will not participate in the clinical study. The randomization information will be concealed until the end of the trial.

### Blinding

2.5

Because of the nature of PPV, doctors and patients will know the grouping information. However, investigator, statisticians, and outcome evaluators will be blinded to group allocation.

### Researchers

2.6

Five investigator will be responsible for data collection. Two supervisors were responsible for monitoring the whole experiment.

### Recruitment

2.7

Patients will be recruited in the department of Emergency and ICU, Guangzhou Panyu central hospital. The poster will briefly provide the trial and treatment details, as well as contact information. Interested participants will be able to contact the researchers directly. We will provide potential participants with detailed information describing the benefits and possible risks of the trial. If they decide to participate, they will ask sign written informed consent informed consent. We will strengthen doctor-patient communication to improve the compliance.

### Patient safety

2.8

The adverse events associated with PPV included severe hypoxemia, pneumothorax and intracranial hypertension. Clinicians will record the occurrence of any adverse events and the intervention will be stopped immediately in case of serious adverse event. The independent safety supervision committee composed of three experts from different fields in Guangzhou Panyu central hospital has the right to terminate the study.

## Interventions

3

### Basic treatment

3.1

All patients will be endotracheally intubated and mechanically ventilated with tidal volume 6 ml/kg (ideal body weight), inspiratory to expiratory ratio 1:2–1:3, respiratory rate less than 20 times/min. And PEEP and FiO2 will be adjusted according to the ARDSnet protocol.

### The control group

3.2

The patients in the control will undergo mechanical ventilation in the 0°prone position for 16 hours a day and turning over every 2 hours. we will remove the electrodes in the anterior chest area and paste hydrocolloid dressings on the clavicle and the anterior superior iliac spine. The electrode will be sticked on the back.

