### The test group

3.3

The patients in the test group will undergo mechanical ventilation in the 0°prone position for 2 hours, then tilted 45° towards prone to the left for 2 hours and tilted 45° towards prone to the right for 2 hours, and returned to 0 ° prone position finally. This cycle will last for 16 hours.

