#### Combined treatment regulations

3.4.1

During study, it is forbidden to use PPV in other positions.

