#### Primary outcome

3.5.1

The primary outcome will be the incidence of PI. Outcome indicators will be collected at day 7 of PPV.

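### Hydrocolloid dressings and anterior electrode removal are specified for the control arm only, so read literally the arms differ in skin protection as well as tilt

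*Protocol article*

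**What the plan says.** Section 2.1 of the protocol article defines the randomised contrast as 45° against 0° prone position ventilation (PPV). Section 3.5.1 sets the endpoint: "The primary outcome will be the incidence of PI", collected at day 7. Section 2.3 plans on "the incidence of 7-day PI in the control group and the test group will be 42.7% and 22.7%, respectively".

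Care is described in four places:

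- **3.1 Basic treatment** is the section addressed to everyone. It opens "All patients will be endotracheally intubated and mechanically ventilated with tidal volume 6 ml/kg" and covers intubation and ventilator settings only.
- **3.2 The control group** gives 0° prone for 16 hours a day with turning every 2 hours, and adds "we will remove the electrodes in the anterior chest area and paste hydrocolloid dressings on the clavicle and the anterior superior iliac spine". The electrode goes on the back instead.
- **3.3 The test group** gives a sequence of positions only: 2 hours at 0° prone, 2 hours tilted left, 2 hours tilted right, "and returned to 0 ° prone position finally. This cycle will last for 16 hours".
- **3.4.1 Combined treatment regulations** contains one rule: "During study, it is forbidden to use PPV in other positions".

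Section 2.5 says that the investigator, the statisticians and the outcome evaluators will be blinded to allocation.

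**The concern.** Dressings over bony points that bear weight in the prone position are a plausible measure against PI, and PI is the primary outcome. If only control patients receive them, randomisation assigns two things at once, tilt and skin protection, and the primary comparison cannot separate them.

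The direct effect of one-arm dressings would most likely work against 45°, because the comparator is better protected. A useful technique could then look weaker than it is, or fail to show a benefit.

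There is a second route to bias. Dressings present in one arm only can be seen when the skin is examined, so they could reveal allocation to evaluators who are meant to be blinded. That bias could run either way, so the net direction is not certain.

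**Working it through.** **Step 1. Compare the care stated for each arm.**

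| Element | All patients (3.1) | Control (3.2) | Test (3.3) |
|---|---|---|---|
| Ventilator settings | stated | – | – |
| Position schedule | – | stated | stated |
| Hydrocolloid, clavicle and anterior superior iliac spine | – | stated | – |
| Anterior electrodes removed, electrode on back | – | stated | – |

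Section 3.3 does not refer back to 3.2, and 3.4.1 restricts positions only. No section extends the skin measures to the test arm.

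**Step 2. Does the reason for the dressings apply to the test arm?** Sixteen hours is 16 / 2 = 8 two-hour slots. Repeating 0°, left, right puts slots 1, 4 and 7 at 0°: 3 × 2 = 6 hours. If the closing return to 0° is its own two-hour slot (0°, left, right, 0°), 4 of the 8 slots are at 0°: 4 × 2 = 8 hours. Test patients therefore spend about 6 to 8 of the 16 hours in the position for which the dressings are prescribed.

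**Step 3. Reproduce the planned sample size.** Inputs from 2.3: 0.427 and 0.227, alpha 0.05, and 0.10 read as beta (its symbol is illegible in the text). Section 3.10 makes the tests two-sided. With the unpooled normal approximation:

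n = (1.960 + 1.282)² × (0.427 × 0.573 + 0.227 × 0.773) / 0.200² = 110.4, rounded up to 111 per arm.

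This matches the plan. The plan recruits 268 / 2 = 134 per arm to allow for loss.

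**Step 4. Illustrate the size.** The article gives no dressing effect, so these two inputs are assumptions: 25% of PI arise at the two covered sites, and dressings cut PI there by 20-40%. The relative cut in overall risk is k = 0.25 × 0.20 = 0.05 to 0.25 × 0.40 = 0.10. Assume also that 42.7% is a rate without dressings.

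Control rate with dressings:

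- k = 0.05: 0.427 × 0.95 = 0.406, difference 0.179
- k = 0.10: 0.427 × 0.90 = 0.384, difference 0.157

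Power of the pooled two-proportion test, two-sided 5%, is Φ[(d − 1.960 × √(2p̄(1 − p̄)/n)) / √((p₁(1 − p₁) + p₂(1 − p₂))/n)], where d = p₁ − p₂ and p̄ is the mean of p₁ and p₂. For the plan at n = 111: (0.200 − 1.960 × 0.0630) / 0.0615 = 1.245, so power is 0.893. The rest follow in the same way:

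| Scenario | 111 per arm | 134 per arm |
|---|---|---|
| As planned, 0.427 v 0.227 | 0.893 | 0.941 |
| Dressings in control only, k = 0.05 | 0.821 | 0.886 |
| Dressings in control only, k = 0.10 | 0.723 | 0.802 |
| Dressings in both arms, k = 0.05 | 0.869 | 0.924 |
| Dressings in both arms, k = 0.10 | 0.842 | 0.903 |

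In the rows for both arms, each rate is multiplied by (1 − k).

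**The case against.** The best defence is that the literal reading is not the intended one. Section 3.2 may describe preparation for the prone position once, at first mention, leaving 3.3 to give only what differs. Read literally, the test arm would have no electrode instruction at all, which suggests an omitted repetition. The article is also a condensed account of a fuller protocol, it nowhere says that test patients go without these measures, and one hospital's staff may well prepare every prone patient alike. All of this is plausible, and practice may be sound. It does not settle the text: the article has a section for shared care and put these measures under one arm instead, so this is more than silence.

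Second, if dressings favour the control arm, a significant benefit for 45° would have been shown despite them. That holds for their direct effect, and attribution suffers most for a null or adverse result. The size of any benefit would still mix two measures, and possible unblinding could push either way.

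Third, the power figures rest on assumed inputs. This stands. With an overall cut of only 2.5%, one-arm power at 111 per arm is 86%. If 42.7% already describes a dressed control group, no power is lost. The figures illustrate the point and do not carry it.

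Fourth, bedside staff will see the tilt anyway, and moving electrodes to the back may be ordinary monitoring practice. Both are fair, but the dressings alone are enough to make the point.

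**Conclusion.** The concern holds for the text as written: the protocol assigns a plausible PI-preventive measure to the control arm only, in a trial whose primary outcome is PI. Followed exactly, it does not isolate tilt. It should be fixed. Confidence is medium, because the wording is clear about placement but actual practice is unknown.

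The size cannot be derived from the article. If dressings lower overall PI risk by 5-10% and the planned control rate excludes them, the expected difference falls from 20.0 to 17.9-15.7 points. Power then falls from 89% to 82-72% at 111 per arm, or from 94% to 89-80% if all 134 per arm are analysed. If the planned rates already reflect arm-specific care, the harm is limited to attribution and possible unblinding.

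**What to change.** Move the electrode and skin-protection sentences from 3.2 to 3.1 Basic treatment, so that they apply identically to both arms.

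The cost is a short amendment and a few extra dressings, or a text change alone if both arms already receive them. Section 4.1 says recruitment is under way, so dressing use in patients already enrolled should be recorded by arm.

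Dressing both arms may lower event rates slightly. Under the same assumed 5-10% cut, power would be about 87-84% at 111 per arm, or 92-90% at 134. That is somewhat below plan, but above the corresponding figures with dressings in one arm only.
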